## Abstract

**Background:**

Attention Deficit/Hyperactivity Disorder (ADHD) is associated with a diversity of impairments and Oppositional Defiant Disorder (ODD) is a very frequent comorbidity. Parent Training, as an evidence-based intervention, seems effective in reducing externalizing/disruptive behaviors, possibly leading to a better prognosis. This clinical trial aims to evaluate the effectiveness of an online parent training model as a complementary treatment for ADHD and ODD.

**Methods:**

Patients and their families will be screened upon their entry into the Research Center of Impulsivity and Attention (NITIDA) at UFMG—Brazil. Ninety families whose children are male, between 6–12 years old, and have significant externalizing symptoms and whose primary caregiver have complete high school education will be invited to participate. Families will be randomized (1:1) into 03 groups: 1) standard care; 2) standard care + face-to-face parent training; 3) standard care + online parent training. Interventions are analogous, differing only in delivery format. In the face-to-face format, the intervention will be conducted by a specialized therapist and the online format will be carried out through a platform. There will be six sessions/modules, arranged on a weekly basis. Measures of externalizing symptoms, parental and children quality of life, parental stress and parenting style will be collected at baseline and after the intervention.

**Discussion:**

This clinical trial intends to verify the effects of a new, online, model of an evidence-based intervention, which would allow a wider access in the Brazilian context.

**Trial registration:**

Registered on Brazilian Registry of Clinical Trials (ReBEC). Number: RBR-6cvc85. July 24^th^ (2020) 05:35 pm.

## Introduction

### Background and rationale

#### Background and rationale

Attention Deficit/Hyperactivity Disorder (ADHD) is one of the most common neurodevelopmental disorders in childhood, affecting more than 5% of the world’s child population [1]. The disorder is characterized by symptoms of inattention-disorganization, hyperactivity and impulsivity, in addition to high clinical heterogeneity in terms of the course of symptoms and functional outcomes [2]. ADHD is associated with functional, social and academic impairments and the need for treatment increases for each additional symptom [3]. ADHD is a chronic disorder of development and should not be seen only as a disorder that affects children’s behavior and learning [4]. The cumulative impairment of ADHD throughout life is considerable, including a higher mortality rate plus an increased risk of suicide, social adversity, high rate of comorbidities with others mental disorders (~ 84%) such as substance abuse, anxiety and mood disorders, personality disorders and disruptive disorders [4, 5]. Compared to children with typical development, children with ADHD usually have greater social disadvantages (lower family income, lower education and higher dropout rates, etc.) [6]. The individual losses of ADHD also translate into public costs in the field of education (special education, interventions with occupational therapy, speech therapy and physical education, school retention, psychological counseling due to disciplinary incidents at school etc.) and health care (primary care, pharmacological treatment, emergency services, care for behavioral and emotional problems, etc.) [7]. Another public cost is related to judicial problems of ADHD adolescents, leading to institutionalization. For adults, the costs are associated with loss of income and productivity at work, which increases with ADHD severity, lower salaries compared to healthy adults, difficulty in finding and maintaining a job, higher rate of absenteeism at work due to health reasons, difficulties in relationships with colleagues, in addition to more use of health services and problems with the law due to criminal behavior [7–9].

Disruptive Behavior disorders are the most easily identifiable conditions among those coexisting with ADHD, as they involve notable behaviors such as "tantrums," physical aggression, excessive argumentation, theft and other forms of challenge and resistance to authority [10]. The disruptive disorder most often coexisting with ADHD is Oppositional Defiant Disorder (ODD), which can reach 50% of cases [10]. Children with externalizing behaviors are more sensitive to the effects of hyper-reactive parenting [11]. The most negative interaction about the child seems to be elicited by the inherent externalizing problems [12, 13]. Children with ADHD usually talk too much, are more distracted, demanding, sulky and uncooperative which is more challenging for parents and makes them more stressed [14]. Parental stress, in turn, contributes to the adoption of negative parenting strategies such as authoritarianism, as well as disruptive problems in children and inefficient implementation of interventions [15–17]. The severity of behavioral and disruptive problems in children is closely associated, therefore, with parental problems, and the family environment may be a determining factor in the prognosis and presence of comorbidities [18]. These disruptive behaviors cause long-term damage, being associated with negative and poorly adaptive outcomes in adult life such as risky sexual behavior, worse academic performance and professional achievement, greater number of infractions and car accidents, in addition to the presence of comorbidities such as anxiety and substance abuse [18]. Effective interventions in childhood, resulting in the control of these behaviors, promote a significant reduction of these losses in adulthood [19]. In addition to drug treatment, Parent Training (PT) has long been considered extremely effective in reducing externalizing / disruptive behaviors [20, 21].

Among existing Parent Training models, the Kazdin method is widely used [21, 22]. It consists of 12 meetings, where social learning techniques are taught to parents to change their children’s behavior and communication and integration patterns at home [22]. It is based on four pillars: conceptual vision on how to change problems, set of techniques, development of specific skills and treatment assessment [22]. The objectives of PT are: to increase knowledge about the causes of children’s bad behavior, to teach parents to pay attention to children’s behavior, also discovering its positive aspects, to improve the efficiency of parents’ authority to deal with your children’s bad behavior, increase child’s cooperation, distend relationships and promote family harmony [22]. This program is entirely based on behavioral science. Ciesielski, Loren and Tamm [23] observed that a behavioral parent training program significantly reduced refusal behaviors, especially in relation to daily tasks, homework, meals and interaction with peers. In addition, the program was effective in reducing parental stress [23].

In a Cochrane summary, Trevedi observed an improvement in parents’ mental health related to group parent training programs [24]. In addition, the intervention reduced symptoms of anxiety, depression, guilt and anger and perceived stress in parents. There was also an increase in satisfaction with the relationship with the partner and a sense of parental confidence. The study pointed to short-term improvement, showing the need for some type of maintenance [24]. A randomized clinical trial showed PT’s effectiveness in reducing ADHD symptoms and family tension, and improving parental self-efficacy. The positive effects remained for 36 weeks after treatment and the findings were restricted to parental reporting [25]. A review study on parent training interventions in ADHD, Zwi and collaborators observed a positive effect on children’s behavior and a significant reduction in parental stress, as pointed out in other studies [26]. Despite this, the review highlights the low methodological quality of the included studies. In another review, regarding treatment available and recommended for ADHD, psychosocial interventions still present inconsistent evidence, especially in reducing symptoms of ADHD [27]. The review draws attention to the need for new studies that combine pharmacological intervention with other types of treatment, with a lack in the literature, especially concerning adolescent groups [27].

Several factors are associated with heterogeneity in the clinical response to PT. Among these are severe psychiatric comorbidities in patients with ADHD, and severe psychiatric conditions diagnosed in primary caregivers, in addition to severe social adversity in the home context, such as deprivation of basic rights [22]. Low socioeconomic status is strongly related to negative outcomes in children with ADHD, such as low school performance [28] and higher frequency of Oppositional Defiant Disorder (ODD) as a comorbidity [29]. Despite inconsistent findings, several studies have promoted the effectiveness of PT [23]. However, PT is a high-cost intervention and, thus, not commonly available in the public sphere in low-middle income countries such as Brazil. With a high prevalence, ADHD and ODD affect a large number of children whose families have low socioeconomic status, requiring a viable and low-cost alternative.

Some recent studies evaluated the feasibility of Parent Training implemented through online platforms. In a systematic review on the PT in digital format, several programs were evaluated for their effectiveness, considering that four out of seven programs were originally taught in person and were adapted to the digital format [30]. Of the studies that reported positive behavioral outcomes, the average effect size for parents’ results was d = 0.46 and for results related to children’s behavior, it was d = 0.61 [30]. Rabbitt and colleagues compared two groups of parents, whose children had conduct problems, who went through PT, one undergoing interventions exclusively in person and the other with very little contact between parents and therapists [31]. In both cases, the children showed a significant improvement in terms of functionality, adaptation and reduction of externalizing problems. The study points out, however, that parents reported better satisfaction with the module entirely in person, despite similar effects in all post-treatment assessments [31]. Högström and his collaborators also evaluated the effectiveness of a PT program administered online [32]. The results show a significant decrease in children’s disruptive behaviors, over 18 months, since the beginning of the intervention that lasted 10 weeks. However, parenting skills seemed to worsen over time, demonstrating the need for some type of training maintenance [32]. A meta-analysis study demonstrated that the digital format of parent training promotes significant improvement in children’s behavior when compared to those without treatment [33]. The study also pointed out that interactive computer programs were more effective than non-interactive ones [33]. Another review study demonstrated that the digital format, with reduced professional support, has similar evidence to the traditional format of parent training [34]. In addition, when compared to an untreated group, self-directed programs achieved significant improvements in the child’s behavior (children <9 years, d = 0.47–0.80, 4 studies; and adolescents d = 0.17, 0.20, 2 studies) [34]. Preliminary indicators also suggested that improvements in technology may increase the involvement and results of standard treatment [34].

Considering the functional impact that disruptive behaviors add to ADHD, we will investigate the feasibility and effectiveness of a fully virtual parent training program when compared to face-to-face PT. Moreover, to assess the importance of this treatment, outcomes of intervention groups will be compared with a naive third group of children. The present study protocol has the potential to develop an accessible intervention technology aimed at families, of low/medium socioeconomic level, of children with serious externalizing problems. Socioeconomic level and organization of family environment are moderators of ADHD symptoms, demonstrating the importance of the interaction between genetics and environment in the clinical presentation/severity of the disorder [35]. This relationship can also occur due to the difficulty of access to health services, faced by low-income families. The trial, therefore, can reach vulnerable and unassisted populations. Although PT is costly in economic and human resources, it seems to have important and positive effects on the development of children [23].

#### Choice of comparators

Parent training as proposed by Kazdin is originally delivered in face-to-face format, being a well-consolidated and evidence-based program [22]. Thus, the online format is a new proposal and its effectiveness in relation to the traditional format should be investigated. Likewise, the potential benefit of an online PT in relation to conventional treatment, which would not include this type of intervention, should be explored, since the program can bring benefits regardless of the effectiveness in relation to the traditional delivery format. All patients will be under psychiatric follow-up at the Research Center of Impulsivity and Attention (NITIDA) and therefore will be receiving conventional treatment, which especially includes pharmacological treatment, at medical discretion, according to the clinical protocol. One group will receive only the usual care, and the other two will be submitted to PT, one in online format and the other in face-to-face format.

### Objectives

The objectives of this randomized clinical trial are: Investigate whether a behavioral parent training program, adapted from the model proposed by Alan Kazdin [22], is effective as a complementary treatment for ADHD and ODD, reducing externalizing symptoms; Investigate the effects of two modalities of parent training (online and face-to-face) on 1) externalizing symptoms reduction, 2) on childrens’ and parents’ quality of life, 3) on parenting style and 4) on stress perceived by the main caregiver, by comparing results before and after the intervention, in each of the modalities and between the modalities, checking out if the effects are similar; Evaluate the effects of parent training in both modalities (online and face-to-face) in short term; Evaluate if there is a moderating effect of the parents’ intelligence, schooling, socioeconomic level, and symptoms of depression, anxiety and ADHD, on intervention response, in each of the parent training modalities (online and face-to-face); Evaluate if there is a moderating effect of the child’s age and school performance on intervention response, in each of the parent training modalities (online and face-to-face).

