#### Concomitant care

Treatment as usual will be delivered for all patients, including drug treatment if there is a clinical indication (at medical discretion, according to the clinical protocol). The treatment can also include speech therapy and occupational therapy, if there is a clinical indication. Other behavioral interventions concurrently will not be allowed.

Although the psychiatric consultations offered by Research Center of Impulsivity and Attention (NITIDA) start at the same time as the first assessment before behavioral intervention, some children may eventually already be on medication or other non-pharmacological treatment. The study will report these treatments, but only participants with another behavioral intervention at the same time will be excluded.

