## Methods: Data collection, management, analysis

### Data collection methods

#### Data collection methods

An initial screening will be carried out by the outpatient team, trained in evaluation procedures by a specialist. In this screening, general data important to the research, such as the parents’ psychiatric history, for example, will be collected through an extensive anamnesis. In addition, the child’s psychiatric screening will be carried out through the K-SADS-PL, an interview based entirely on the diagnostic criteria of the latest edition of the DSM [10, 37]. Intelligence tests (matrices) will be applied to the child and the primary caregiver, both validated and with Brazilian normative data [43, 44].

After the screening, the included participants will undergo a first trial assessment, including a battery of scales that will be completed in the presence of an evaluator, on a notebook. The scales are self-reported (parents’ behavior; items 1, 2, 3, 4 and 5) or refer to the child’s behavior, according to the parents’ report (items 6, 7 and 8), besides the Brazilian Economic Classification Criterion [45].

ASRS—Adult Self-Report Scale (parents ADHD symptoms) [46].Depression, Anxiety and Stress Scale (DASS) [47].Perceived Stress Scale [48, 49].Parenting Styles and Dimensions Questionnaire (PSDQ) [38].World Health Organization Quality of Life abbreviated measure [41, 50].MTA-SNAP (children ADHD and ODD symptoms) [51].The Child and Adolescent Behavior Inventory (CABI) is a questionnaire useful for the preparation of screening for clinical evaluation [52].Kidscreen-52 to evaluate the quality of life of children [42].

After the participant completes the intervention, or the waiting time (six weeks, for the control group), the K-SADS will be reapplied and a battery of scales containing the same instruments (with the exception of the ASRS and DASS) must be completed by the main caregiver.

The interval between the pre-assessment and the beginning of the intervention, as well as the end of the intervention and the execution of the post-assessment, will be as small as possible, and cannot exceed a maximum period of 60 days. The deadline was considered for project feasibility, taking into account the need for flexibility in scheduling between the team and parents.

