### Statistical methods

#### Outcomes

The main analysis strategies will involve techniques for group comparison (ANOVA etc.), analysis of repeated measures (mixed models, GHG etc.), as well as correlation and regression to verify the association between variables. Techniques will be chosen depending on data distribution. If necessary, depending on the sampling power, we will employ techniques resampling.

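### The Objectives assess the two training formats by within-arm change and against each other, without naming the usual-care arm that the rest of the protocol intends as comparator

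*Protocol article*

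**What the plan says.** In the Objectives, the effects of the two formats on symptoms, quality of life, parenting style and caregiver stress are to be investigated "by comparing results before and after the intervention, in each of the modalities and between the modalities, checking out if the effects are similar". That names two comparisons: pre-post inside each training arm, and online against face-to-face. The two moderator objectives (caregiver intelligence, schooling, socioeconomic level and symptoms; child age and school performance) concern a moderating effect "on intervention response, in each of the parent training modalities (online and face-to-face"). Group 01 appears in none of these. The first objective, whether training works as a complementary treatment, names no comparison.

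Other sections do bring in usual care. Background and rationale says "outcomes of intervention groups will be compared with a naive third group of children". Choice of comparators says "the potential benefit of an online PT in relation to conventional treatment, which would not include this type of intervention, should be explored". Statistical methods (Outcomes) is generic: "The main analysis strategies will involve techniques for group comparison (ANOVA etc.), analysis of repeated measures (mixed models, GHG etc".

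Three design facts bear on within-arm change. Under Concomitant care, "the psychiatric consultations offered by Research Center of Impulsivity and Attention (NITIDA) start at the same time as the first assessment before behavioral intervention", and Interventions gives these consultations, with drugs if indicated, to all three groups. Eligibility requires externalizing symptoms. Under Data collection methods, "the child’s psychiatric screening will be carried out through the K-SADS-PL"; the same interview is a primary outcome instrument and is repeated afterwards.

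**The concern.** Change within a training arm is not an estimate of the training effect. It adds together the training, the psychiatric care that begins at the same time, regression to the mean in children selected for symptoms, and the natural course. The online versus face-to-face contrast is randomized, but it cannot supply the missing reference: two formats that both add nothing to usual care will look alike. Improvement in both arms plus no difference between them could be read as two effective, similar treatments, and the Trial design section's equivalence label invites that reading.

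Moderation has the same difficulty. If response is examined only inside a training arm, a variable that predicts improvement in any child looks the same as one that changes the benefit of training. A prognostic factor could then be reported as a reason to offer or withhold online training.

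**Working it through.** The protocol gives no error rate or power for this comparison, so there is no stated figure to reproduce. The check asks how often each comparison is significant when training has no effect but all arms improve equally.

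**Inputs**
- n = 30 per arm (Interventions).
- Pre-post correlation r = 0.4, 0.6 and 0.9. These are the values in Sample size, given there as a covariance of 0.4 and ICCs of 0.6 to 0.9; reading them as pre-post correlations is an assumption.
- Two-sided alpha 0.05 (assumed; not stated).
- Common improvement g in SD units, identical in all arms (assumed; the documents give no figure): 0.2, 0.3 and 0.5.
- True training effect: zero.

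**Within-arm paired t-test**

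The SD of change is √(2(1−r)), so the standardized change is dz = g/√(2(1−r)) and the noncentrality is dz·√30, on 29 degrees of freedom (critical value 2.045).

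- g = 0.2, r = 0.4: dz = 0.2/√1.2 = 0.183; noncentrality 1.00; significant in 16%.
- g = 0.2, r = 0.9: dz = 0.2/√0.2 = 0.447; noncentrality 2.45; 66%.
- g = 0.5, r = 0.4: dz = 0.456; noncentrality 2.50; 68%.
- g = 0.5, r = 0.6: dz = 0.559; noncentrality 3.06; 84%.
- g = 0.5, r = 0.9: dz = 1.118; noncentrality 6.12; about 100%.

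| Common improvement | r = 0.4 | r = 0.6 | r = 0.9 |
|---|---|---|---|
| 0.2 SD | 16% | 22% | 66% |
| 0.3 SD | 31% | 43% | 94% |
| 0.5 SD | 68% | 84% | ~100% |

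**Contrast with control**

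In a simulation of 20,000 runs under the same conditions, the t-test comparing change in a training arm with change in Group 01 was significant in about 5% of runs at every g and r. The common improvement cancels.

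**Both arms improve and look similar**

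At g = 0.5, both training arms showed a significant pre-post change in 46% (r = 0.4), 71% (r = 0.6) and 100% (r = 0.9) of runs, while the two arms differed significantly in only about 5%.

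**Moderators**

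Here a variable is correlated ρ with change, equally in the training and control arms, so it is purely prognostic (ρ is assumed; 20,000 runs, 30 per arm).

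| ρ | Within-arm test significant | Interaction with control significant |
|---|---|---|
| 0.2 | 19% | 5% |
| 0.3 | 37% | 5% |
| 0.5 | 83% | 5% |

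**The case against.** The strongest reply is that the control comparison is planned. The background says the training groups will be compared with the third group, the choice of comparators wants online training examined against conventional treatment, the design is randomized and controlled, Group 01 is reassessed after a six-week wait, and the methods list begins with group comparison. All of this stands. A reader might infer from the Objectives that effectiveness will be judged by before-after change alone, with usual care ignored, so that both formats would be declared effective under the plan as written. The documents do not support that inference. The quoted objective also contains a randomized comparison between the formats.

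The moderator wording likewise neither says before-after nor excludes Group 01; an interaction against control would fit it. Analysis inside each training arm is the likely reading, not an explicit statement, and the form of the model may be left to an analysis plan that is not shown.

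It is also fair that improvement in all arms is plausible rather than certain. Drugs are given only if indicated, and some children may already be medicated at entry. The screening-instrument argument applies to the K-SADS-PL; the MTA-SNAP-IV is completed after screening, which weakens regression to the mean for that measure. The size of the common improvement is assumed throughout.

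What these replies leave untouched is that the one sentence stating how the formats' effects will be investigated omits the reference arm, and the methods section fixes no contrast to correct it.

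**Conclusion.** The point holds as a mismatch within the protocol. The Objectives name within-arm change and online versus face-to-face for the effects of the formats, and frame moderation inside each training arm, while other sections intend a comparison with usual care. Within-arm change cannot isolate a training effect here, and similarity of the two formats does not establish that either works. On the likely reading of the moderator objectives, prognosis and moderation cannot be separated.

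The size depends on the assumed common improvement: false-positive rates of about 16–66% at 0.2 SD and 68–100% at 0.5 SD for the within-arm test, against about 5% for the contrast with control. These rates describe what happens if the within-arm test is taken as evidence of effect; they are not a forecast for the trial. The 5% for the control contrast also presumes that randomized participants stay in the analysis. The rule excluding non-completers (Analysis population and missing data) affects that and is a separate matter.

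**What to change.** Align the Objectives with the background and the choice of comparators:

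- Define the effect of each training format as its baseline-adjusted difference from Group 01 at the post-intervention assessment.
- Keep the online versus face-to-face contrast as its own question.
- Treat change within each arm as descriptive, not as evidence of effect.
- Define moderation as arm-by-moderator interactions in one model with all three arms and Group 01 as reference. Label these exploratory and report estimates with confidence intervals.

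The cost is wording: Group 01 is already randomized and reassessed, so no new data are needed. The downside is that interaction estimates will be imprecise with 30 per arm, and the report should say so.
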